#### Metagenomic library construction and sequencing

The Nextera XT DNA Library Preparation Kit (Illumina, San Diego, CA, USA) will be used for metagenomic library construction. The amplicon tagment mix (ATM) in Nextera XT, which includes the enzyme used for tagmentation, will be diluted 1:10 in nuclease-free water for library construction using 1 to 100 pg input DNA. Each 20 μL of the tagmentation reaction mixture consists of 10 μL TD buffer, 5 μL of input DNA, and 5 μL of diluted ATM. PCR cycles for library construction will be 12, 14, 17, and 20 cycles for 1000, 100, 10, and 1 pg DNA, respectively, following the manufacturer’s protocol. The manufacturer recommends 12 cycles of the PCR reaction for no less than 1 ng input DNA. Amplified libraries will be purified using AMPure XP (Agencourt, Brea, CA, USA). The quality of the purified libraries will be assessed using an Agilent High Sensitivity DNA Kit on an Agilent 2100 Bioanalyzer (Santa Clara, CA, USA). The sequencing libraries will be further quantified using the KAPA Library Quantification Kit. Metagenomic libraries will be mixed with PhiX Control v3 (Illumina) at a ratio of 9:1 and sequenced with an Illumina MiSeq Reagent Kit v3 (600 cycles).

All samples to be analyzed will be combined in a pool before starting the massive sequencing. The latter will be done with the MiSeq apparatus (Illumina).

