#### Data processing for metagenomic libraries

Metagenomic reads will be subjected to adaptor clipping and quality trimming using Trimmomatic v0.33 [19]. The first three nucleotides with quality scores less than 20 will be cut from the 3′ and 5′ read ends. Reads will be processed using a sliding window method, cutting once the average quality within the window (4 base) fell below the threshold (Q20). Reads with a length of fewer than 100 nucleotides will be then removed. Low-complexity reads will be filtered out using PRINSEQ version 0.20.4 [20]. PCR duplicates will be removed with Picard version 2.8.0 (http://broadinstitute.github.io/picard). The processed high-quality and clean reads in each library will be used in subsequent analyses. In the community analysis based on metagenomic sequences, small subunit (SSU) rRNA gene sequences will be identified using Metaxa2 software [21]. Taxonomy assignments will be performed based on the results of a BLAST search against the SILVA123 database [22], using the MEGAN program [23] with the following settings: Min Support 1, Min Score 50, Max Expected 1xe^− 5^, Top Percent 10.0. SSU rRNA gene community compositions were compared among the metagenomic libraries.

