##### Quality controls

Several types of control experiments will be performed in parallel with the experimental samples. A pooled matrix sample, generated by taking a small volume of each experimental sample, will serve as a technical replicate throughout the extracted data set. Water aliquots will serve as process blanks. Moreover, a cocktail of QC standards carefully chosen not to interfere with the measurement of endogenous compounds will be spiked into every analyzed sample. This will allow instrument performance monitoring and aid in the chromatographic alignment. The instrument variability will be determined by calculating the median relative standard deviation (RSD) for the standards that will be added to each sample before injection into the mass spectrometers (MS). The entire process variability will be determined by calculating the median RSD for all the endogenous metabolites (i.e., non-instrument standards) present in 100% of the pooled matrix samples. The experimental samples will be randomized across the platform run with the QC samples spaced every 5 or 10 injections to verify overall assay performance [24]. The internal standards will be used to measure the instrument variability and will have a median RSD of 3%. Additionally, the total process variability will be 8%.

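### Sequencing at picogram input accepts a taxon on one read, with no blank or contaminant filter described, so contaminant reads may be reported as microbiota

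*Protocol article*

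**What the plan says.** All references are to the protocol article.

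- **Input and amplification** (Metagenomic library construction and sequencing). The tagmentation mix "will be diluted 1:10 in nuclease-free water for library construction using 1 to 100 pg input DNA". The cycle schedule is "PCR cycles for library construction will be 12, 14, 17, and 20 cycles for 1000, 100, 10, and 1 pg DNA, respectively". The same paragraph notes that "The manufacturer recommends 12 cycles of the PCR reaction for no less than 1 ng input DNA".
- **Taxon calling** (Data processing for metagenomic libraries). Reads pass adaptor, quality, length, low-complexity and PCR-duplicate filters. Taxonomy is then assigned "using the MEGAN program [23] with the following settings: Min Support 1, Min Score 50", together with an E-value cap and a top-percent setting.
- **Controls in the sequencing arm**. The only one named is a run control: "Metagenomic libraries will be mixed with PhiX Control v3 (Illumina) at a ratio of 9:1".
- **Controls in the metabolomic arm** (Quality controls). "Water aliquots will serve as process blanks", and "The experimental samples will be randomized across the platform run with the QC samples spaced every 5 or 10 injections".
- **Source of breast tissue** (Biological samples). Cases give tissue 3–5 cm from the tumour. Controls give whatever tissue is available at breast reduction or augmentation.
- **Comparison** (Statistical analysis). Relative abundances are compared by Mann-Whitney and communities by PERMANOVA on Euclidean distance.

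**The concern.** Three features combine. Input DNA is very small, so any DNA introduced by kits, reagents or handling can be a material part of a library. One read is enough to call a taxon. None of the listed read filters targets contamination, because contaminant DNA can be good-quality, non-duplicate sequence and will pass them. PhiX shows how the run performed and does not reveal what entered at extraction or library preparation.

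Breast tissue is where this matters most. The Background section notes that it was long presumed sterile, so genuine microbial DNA there is likely to be scarce.

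Two consequences are possible. The reported list of mammary taxa may include organisms that were never in the tissue. If DNA yield or processing batch also differs between cancer-surgery and cosmetic-surgery specimens, the contaminant share will differ too, and the planned tests would register that as a difference in microbiota. That comparison bears directly on the study's hypothesis.

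**Working it through.** The article gives no figure to reproduce on this point. What follows shows when the stated settings matter. Every contaminant mass, read count and alternative threshold below is an assumption.

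**1. Input against the cited recommendation.** 1 ng = 1000 pg. The stated range is therefore 1000/100 = 10 times to 1000/1 = 1000 times below the input for which the article says 12 cycles are recommended.

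**2. Contaminant share of total library DNA.** Share = c/(c + s), where s is sample input and c is assumed contaminant mass.

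| Input s | c = 0.1 pg | c = 1 pg | c = 10 pg |
|---|---|---|---|
| 1 pg | 9% | 50% | 91% |
| 10 pg | 1% | 9% | 50% |
| 100 pg | 0.1% | 1% | 9% |
| 1000 pg | 0.01% | 0.1% | 1% |

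The problem sits mainly at the low end of the range. These are shares of all DNA in the library. No host-depletion step is described, so s includes the woman's own DNA. If only a fraction f of s is microbial and the contaminant is all microbial, the share of the microbial community is c/(c + f·s). Neither c nor f is given, so the table cannot be read as a share of the microbiota.

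**3. Probability that a contaminant taxon is called in a library.** With a Poisson mean of λ contaminant reads, P(called) = P(X ≥ k). At k = 1 this is 1 − exp(−λ). The value k = 5 is only an example of a higher threshold.

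| λ | k = 1 (as planned) | k = 5 |
|---|---|---|
| 0.1 | 9.5% | <0.01% |
| 0.5 | 39.3% | 0.02% |
| 1 | 63.2% | 0.4% |
| 2 | 86.5% | 5.3% |
| 5 | 99.3% | 56.0% |

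A higher threshold removes sporadic contaminants but not abundant ones (last row), so a threshold alone does not replace blanks.

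**4. Weight of one read.** One stray read among N microbial SSU reads is 1/N of the community. If N were 20 that is 5%, and if N were 1 it is 100%. N is not given.

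**5. Effect on a group comparison.** Take 100 per group and suppose mean contaminant reads differ twofold between groups with identical true microbiota. The chance of a significant difference in detection (two proportions, two-sided 0.05, normal approximation) is:

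| Mean reads, group A v B | Detected at k = 1 | Power, k = 1 | Power, k = 5 |
|---|---|---|---|
| 0.1 v 0.2 | 9.5% v 18.1% | 42% | about 3% |
| 0.25 v 0.5 | 22.1% v 39.3% | 76% | about 3% |
| 0.5 v 1 | 39.3% v 63.2% | 93% | 8% |
| 1 v 2 | 63.2% v 86.5% | 97% | 55% |

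In the first two rows at k = 5 the detection rates are near zero and the approximation is poor; read those entries as no real inflation. The planned test uses relative abundance, not detection, so this table indicates direction and order of size only. With equal means in both groups there is no false case-control difference.

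**The case against.** The strongest counter-argument is that the article is condensed. Blanks and batch layout are laboratory detail that a full protocol may contain. This stands as far as it goes: a reader might infer that sequencing will be run without negative controls, but the article does not say so. It is silent. The input range and the one-read setting, however, are stated choices, and the described pipeline goes from the read filters straight to taxonomy.

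Other points that stand:

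- The picogram range covers all metagenomic libraries, stool and breast alike, and the cycle schedule reaches 1000 pg. The text does not assign 1 to 100 pg to breast tissue.
- A reader might infer that contamination would go undetected. That is too strong. DNA concentration is measured for each sample (DNA quantification), libraries are quantified, and breast biopsies are cultured with colonies identified by 16S PCR (Evaluation of DNA damage). These allow a partial check.
- A reader might also infer that cases and controls will differ in contaminant share. Nothing in the article shows that DNA yield, fat content or batch differs by group. Matching on hospital and body mass index category, and pooling all samples for sequencing, close some routes. They do not balance DNA yield or extraction batch.
- Extra PCR cycles amplify sample and contaminant together, so they do not in themselves raise the contaminant share, and PCR duplicates are removed.
- Isolated single-read taxa carry little weight in Mann-Whitney or PERMANOVA unless total microbial reads are low. Whether they are low is unknown.

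**Conclusion.** The point holds in a limited form. Picogram input and one-read acceptance are stated, no blank or contaminant filter is described for sequencing, and the article applies blanks and randomised order in its metabolomic arm. Contaminant or misassigned reads may therefore be reported as microbiota, chiefly in breast tissue. They may confound the case-control comparison, but only if biomass or processing differs by group. If contamination is equal in both groups, the result is spurious taxa and not a false association.

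No single size can be given. For 1 pg of contaminant, the share of library DNA runs from 50% at 1 pg input to 1% at 100 pg. For 0.5 contaminant reads per library, the call rate is 39% at the planned threshold. Both rest on assumed inputs.

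**What to change.** - Sequence a reagent-only extraction blank and a library blank with every batch.
- Replace Min Support 1 with a minimum read count set from those blanks.
- Apply a prevalence- or frequency-based contaminant filter before the Mann-Whitney and PERMANOVA comparisons.
- Process each matched case and control in the same extraction and library batch, in random order.
- If the full protocol already provides for blanks, state this and say how they enter the taxon calls.

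The Trial status section says enrolment and analysis continue, so some batches may already have been processed. For any processed without blanks, use a frequency-based filter on measured DNA or library concentration, and report results with and without low-count taxa. This is only a partial substitute, because measured concentration includes host DNA.

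The cost is a few extra blank libraries per batch, a bioinformatic step, and the loss of some genuinely rare taxa. No participant procedure is added.

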### Functionality of the intestinal and mammary microbiota

Microbiota functionality will be investigated with a metabolomic study and by evaluating their capacity to damage the DNA of HeLa cells.

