**Methods:**

We describe a case-control clinical study that will be performed in women between 25 and 70 years of age. Cases will be women diagnosed and surgically intervened of breast cancer (stages I and II). Women with antecedents of cancer or advanced tumor stage (metastasis), or who have received antibiotic treatment within a period of 3 months prior to recruitment, or any neoadjuvant therapy, will be excluded. Controls will be women surgically intervened of breast augmentation or reduction. Women with oncological, gynecological or endocrine history, and those who have received antibiotic treatment within a period of 3 months prior to recruitment will also be excluded. Blood, urine, breast tissue and stool samples will be collected. Data regarding anthropometric, sociodemographic, reproductive history, tumor features and dietary habits will be gathered.

Metabolomic studies will be carried out in stool and breast tissue samples. Metagenomic studies will also be performed in stool and breast tissue samples to ascertain the viral, fungal, bacterial and archaea populations of the microbiota. Quantitation of estrogens, estrogen metabolites and EDCs in samples of serum, urine and breast tissue will also be performed.

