Concerning the influence of microbes on breast cancer, some studies have focused on viruses. Up to 50% of breast tumors are Epstein-Barr positive [11], and human papilloma virus also appears to be associated with breast cancer [12]. In addition, the diversity and composition of the gut microbiota may affect breast cancer risk through the modulation of systemic levels of estrogens and inflammation [13]. In this sense, alterations of microbes able to metabolize estrogens and other endogenous hormones lead to an increment in circulating estrogen levels, which ultimately increase the risk of breast cancer development [14]. Furthermore, a reduced abundance of *Methylobacterium* in breast cancer patients has been correlated with tumors of greater invasive potential [15]. Moreover, exposure to a wide variety of xenobiotics (i.e. endocrine disruptors compounds (EDCs), which are found in routinely used products, lead to an increment of the risk of breast cancer [9]. Indeed, it has been hypothesized that in utero exposure to EDCs plays a role in breast cancer in women later in life [16]. Altogether, this background has drawn the attention of the scientific community in the mammary microbiome direction, albeit studies are still very limited and some of the published results are contradictory [17].

The rationale of our work is that the risk of breast cancer could be associated with the composition and functionality of the mammary/gut microbiota, and that exposure to environmental contaminants (i.e. EDCs) might contribute to alter both the gastrointestinal and mammary microbiota. Consequently, we aim to decipher the correlation among i) the composition of both the mammary and the gut microbiota, ii) the metabolic pathways in which they are involved, iii) the role of EDCs exposure to its alteration, and iv) the risk and progression of breast cancer, which might have broad implications in the prevention, diagnosis, treatment and prognosis of this disease.

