##### Sample preparation

The samples will be prepared using the automated MicroLab STARR (Hamilton Company, Salt Lake City, UT, USA) robot system. For quality control (QC) purposes, a recovery standard will be added to 100 L of the serum samples before the first step in the extraction process. The proteins will be precipitated with methanol by vigorously shaking for 2 min. Next, the samples will be centrifuged to remove the proteins, dissociate the small molecules bound to the proteins or trapped in the precipitated protein matrix, and to recover chemically diverse metabolites (Glen Mills GenoGrinder 2000, Lebanon, USA). Then, the samples will be placed on a TurboVapR (Zymark, California, USA) to remove the organic solvent. For liquid chromatography (LC) analysis, the samples will be stored overnight in nitrogen before preparation. For gas chromatography (GC) analysis, each sample will be dried overnight under vacuum before preparation [24].

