##### Data extraction and compound identification

The raw data will be extracted, and the peaks will be aligned and identified. QCs will be processed using specific hardware and software [25]. The peaks will be quantified using the area-under-the-curve (AUC) calculation. The compounds will be identified comparing the data to library entries of purified standards or recurrent unknown entities. The biochemical identifications will be based on three criteria: the retention index (RI) within a narrow RI window of the proposed identification, an accurate mass match to the library ±0.005 amu, and the MS/MS forward and reverse scores between the experimental data and authentic standards. The MS/MS scores will be based on a comparison of the ions present in the experimental spectrum with the ions present in the library spectrum. Although there may be similarities between these molecules based on one of these factors, the use of all three data points can be utilized to distinguish and differentiate the biochemicals with precision.

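### A case-control difference in the breast tissue metabolome cannot by itself be read as mammary microbial function, because no described step separates host from microbial metabolites

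*Protocol article*

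**What the plan says.** The second aim in *Background* concerns the metabolic pathways in which the mammary and gut microbiota take part. The protocol article then fixes how function is measured: "Microbiota functionality will be investigated with a metabolomic study and by evaluating their capacity to damage the DNA of HeLa cells". The abstract names the sample types: "Metabolomic studies will be carried out in stool and breast tissue samples".

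For the metabolomics, *Data extraction and compound identification* states: "The compounds will be identified comparing the data to library entries of purified standards or recurrent unknown entities". *Statistical analysis* plans a per-metabolite t-test whose two groups are called the intestinal and the mammary microbiota, with thresholds of p 0.05 and q 0.1.

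For sequencing, *Metagenomic library construction and sequencing* states: "The Nextera XT DNA Library Preparation Kit (Illumina, San Diego, CA, USA) will be used for metagenomic library construction". In the community analysis of these reads, "small subunit (SSU) rRNA gene sequences will be identified using Metaxa2 software", followed by taxonomic assignment.

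The second functional readout, the P-H2AX assay, cultures bacteria from breast biopsies and tests them for DNA damage in HeLa cells.

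*Biological samples* gives the tissue sources: a marginal area 3–5 cm from the tumour for cases, and any available tissue from reduction or augmentation surgery for controls.

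**The concern.** A breast tissue extract contains metabolites of the woman's own cells as well as any made by microbes. Library matching tells which compound is present, not which organism made it. The plan nevertheless treats the tissue metabolome as a property of the mammary microbiota, both where it defines function and where it labels the test groups.

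This matters because the two tissue sources are not equivalent. Tissue near a tumour and tissue removed at reduction or augmentation may differ in host metabolism, for example through tumour-field effects or fat content. Followed as written, the plan would let such a difference be reported as altered mammary microbial function, which is one of the study's main aims.

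A smaller, related point concerns the gut. *Background* argues that "alterations of microbes able to metabolize estrogens and other endogenous hormones lead to an increment in circulating estrogen levels". The stool reads could show the genetic capacity for this, but the only use described for them is taxonomic.

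**Working it through.** **Step 1. Trace each data stream to its stated use.**

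- *Breast tissue metabolome:* used as mammary microbiota function. No assignment of a compound to host or microbe appears in the metabolomic sections or in *Statistical analysis*.
- *Stool metabolome:* used as gut microbiota function. The same gap exists, but the objection is much weaker in this material.
- *P-H2AX assay:* bacteria isolated from breast biopsies. The origin is microbial, but the assay covers one function and only culturable bacteria. It says nothing about metabolic pathways.
- *Metagenomic reads:* small-subunit rRNA taxonomy. No functional use is described.
- *Urinary estrogens* (estrone, estradiol and 13 metabolites): related by linear regression to fecal diversity, abundance, and taxa at phylum and family level.

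For the breast, the pathway aim therefore rests on the tissue metabolome alone.

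**Step 2. Illustrate the size.** The plan gives no figure to reproduce here: it states at least 100 cases and 100 controls, with no effect size or power for metabolites. It also gives no host or microbial share of the tissue metabolome. What follows is an illustration under assumptions.

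Inputs: n = 100 per group (*Sample size*) and alpha 0.05 (*Statistical analysis*). Assumed: a case-control comparison of one breast tissue metabolite, a two-sided test, unmatched groups, a normal approximation, and every sample usable.

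*(a) A purely host difference of d SD.* Probability of p < 0.05 = Φ(d√(n/2) − 1.960), with √(100/2) = 7.071.

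- d = 0.3: Φ(2.121 − 1.960) = Φ(0.161) = 0.564
- d = 0.5: Φ(3.536 − 1.960) = Φ(1.576) = 0.942
- d = 0.8: Φ(5.657 − 1.960) = Φ(3.697) = 1.000 to three decimals

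A modest host difference would thus often be declared significant, and nothing in the described analysis would show that it was not microbial.

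*(b) A real microbial difference diluted by host variation.* Let microbes account for a share f of the variance of a tissue metabolite. A microbial difference of 0.5 SD then appears as 0.5√f.

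| f | Observed difference (SD) | Power, 100 per group |
|---|---|---|
| 1 | 0.500 | 94% |
| 0.50 | 0.354 | 71% |
| 0.25 | 0.250 | 42% |
| 0.10 | 0.158 | 20% |
| 0.05 | 0.112 | 12% |
| 0.01 | 0.050 | 5% |

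The number per group for 80% power is 2(1.960 + 0.842)²/(0.25f) = 15.70/(0.25f): 63 at f = 1, 628 at f = 0.10 and 6280 at f = 0.01.

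These are per-metabolite figures at p < 0.05. The q-value rule would normally lower them.

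**The case against.** Several points on the other side stand.

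- The metabolome is not the only functional readout. The P-H2AX assay measures breast bacteria directly.
- The article refers its metabolomic analyses and data processing to earlier publications that are not at hand, so the point can only be that no separating step is described here.
- The aim is framed as correlation, and sampling 3–5 cm away may reduce tumour-field effects. Misattribution is a possibility, not a certainty.

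None of this removes the core. The text states positively that the metabolome measures microbiota function and names the test groups accordingly, so this is more than detail left out of an article.

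Three stronger readings are tempting, and the documents do not support them.

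1. *The breast tissue metabolome is almost entirely host.* This is plausible, but no figure is given. Assuming 10^3 to 10^7 bacteria per gram and 1 pg each, microbes are 10^-9 to 10^-5 of tissue mass, and a tenfold rise would add at most 9 × 10^-5, or 0.009%. Both inputs come from outside the document. Cell mass is also not metabolite share, since secreted products can accumulate. Setting the result against the 8% process variability in *Quality controls* would compare a shift in a group mean with a per-measurement spread.
2. *Microbial gene content is sequenced and then ignored.* The article says that clean reads go into subsequent analyses. It merely describes no functional use. Gene content would in any case show potential rather than realised function, and reads from breast tissue may themselves be largely host, with no host-read removal described.
3. *The microbiome–estrogen link is not studied.* It is, at the level of diversity, abundance and taxa.

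**Conclusion.** The point holds in this form: as described, host and microbial metabolites in breast tissue cannot be told apart, so a case-control difference in that metabolome is not by itself evidence about mammary microbial function. The P-H2AX assay does not fill the gap for the metabolic-pathway aim.

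The conclusion rests on the plan's own definition of function, its group labels and its two different tissue sources, not on any assumed bacterial density. The size is not fixed by the documents and depends on the unknown host difference and microbial share. The measurements remain usable; what does not follow is the planned interpretation. This is a cheap improvement, not a threat to the study as a whole.

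**What to change.** **Main change.** In *Functionality of the intestinal and mammary microbiota* and in *Statistical analysis*, call the breast readout the *breast tissue metabolome* and describe it as a joint host–microbe profile. Limit conclusions on mammary microbial function to two sources: the P-H2AX results, and a list of metabolites that human tissue is not known to make. Fix that list before the case-control comparison is run.

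**Secondary addition.** Annotate the stool metagenomic reads for pathways and for summed estrogen-related gene families, and add these measures to the planned estrogen regressions. Report them as functional potential, limited by read depth. This strengthens the gut side but does not repair the breast tissue problem.

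**Related text to reconcile.** *Sample preparation* refers to serum samples, whereas the abstract places the metabolomics in stool and breast tissue.

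**Cost.** A narrower claim for breast tissue, plus some analyst and computing time. No new samples or assays are needed, and the trial status says that enrolment and analysis are still under way.
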